## **12. Interim analysis**

Interim analysis, if necessary, may be performed by an external statistician if recommended by the local ethical committee. The ethical committee will oversee trial monitoring, which may occur at any time during the trial duration.

## **13. Reporting exploratory biomarkers**

As part of this study, samples derived from all enrolled participants will be stored in the local biobank. Any measurement or analysis used to describe the biological process and its relation to treatment derived from this trial will be linked to the actual treatment received.

## **14. Data analysis**

- a. All data will be pseudo-anonymized. A separate dataset (in Excel) containing participant IDs will be protected. A separate dataset without direct participant IDs will be generated and analyzed using SPSS.
- b. Baseline characteristics will be summarized according to trial group for the ITT populations.
- c. The primary outcome analysis will be focused on the proportion of complete uveitis resolution and the corresponding relative risk between the ATT and control groups. Cox proportional-hazards models will be used to estimate any uveitis resolution between the ATT and control groups. This analysis will be performed at the patient level, where resolution of uveitis is considered when both eyes meet the prespecified criteria. In bilateral

uveitis cases, if one eye shows uveitis resolution but the other does not, as prespecified in the previous section, these participants will be considered to have “no uveitis resolution”.

- d. Pairwise comparisons across experimental arms will be done using a Chi-square test or Fisher’s exact test as appropriate at the 5% significance level for the efficacy endpoint of uveitis resolution at six month time point (see above section). Relative risk will be calculated and presented with 95% confidence interval in the ITT and per-protocol analysis approaches.
- e. Time-to-uveitis resolution will be analyzed using the Cox proportional hazards model and hazard ratio.
- f. For uveitis relapse outcomes, the analysis will include participants with complete uveitis resolution, regardless of follow-up duration. Cox proportional hazards models, along with hazard ratio and Kaplan–Meier estimates, will be used for the analysis.
- g. The number (proportion) of participants experiencing any adverse events will be reported.
- h. Eye-level outcomes will be calculated based on the involved eyes for the presenting uveitis. Therefore, bilateral uveitis presentations will be counted as two eyes.
- i. A *p*-value of less than 0.05 will be considered statistically significant.
- j. All statistical analyses will be performed using IBM SPSS Statistics version 28.0.1.0 (142) for Windows (SPSS Inc.).

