## **6. Other baseline variables**

- xxvi. Age (numerical data)
- xxvii. Laterality of ocular inflammation (categorical data): unilateral or bilateral
- xxviii. Sex (categorical data): male or female
- xxix. Onset (numerical data): days of ocular complaints
- xxx. Chronicity (categorical data): acute or chronic
- xxxi. Previous TB (categorical data): yes or no
- xxxii. Contact TB history (categorical data): yes or no
- xxxiii. Baseline visual acuity (numerical data): Snellen/LogMAR visual acuity, and categorical data: mild visual impairment, moderate visual impairment, severe visual impairment, and blindness.
- xxxiv. IOP (numerical and categorical data): increased or not
- xxxv. Keratic precipitates (categorical data): mutton-fat, fine, or others
- xxxvi. Anterior chamber cells (numerical data)
- xxxvii. The presence of iris nodule (categorical data): yes or no
- xxxviii. Scleral involvement (categorical data): yes or no
- xxxix. Synechia formation (categorical data): yes or no
  - xl. Lens status (categorical data): cataract, pseudophakia, phakic)
  - xli. Vitreous haziness (categorical data): yes or no
  - xl.ii. Vitreous cells (numerical data)
  - xl.iii. Snowball/snowbank (categorical data): yes or no
  - xliv. Retinal vascular changes (categorical data): yes or no
  - xl. v. Optic nerve involvement (categorical data): yes or no
  - xlvi. Retinitis or retinal infiltrates (categorical data): yes or no
  - xl. vii. Choroiditis (categorical data): yes or no
  - xl. viii. Posterior granuloma/tuberculoma appearance (categorical data): yes or no
  - xl. ix. Retinal detachment (categorical data): yes or no
    - l. Macular edema (categorical data): yes or no

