## **7. Sample size calculation**

The sample size is calculated using a formula of two-independent proportion sample size calculation. The primary end point of uveitis resolution at 6 month is used for this sample size calculation.

Based on the Multicenter Uveitis Steroid Treatment (MUST) trial in non-infectious uveitis, the proportion of uveitis patients with active disease at six months following treatment was found to be 44%. A 30% difference in uveitis resolution between the two groups is predetermined. Using a  $Z\alpha$  of 1.96 and a  $Z\beta$  of 0.84 (for a two-sided significance level of 5% and 80% power), the estimated sample size required for each treatment group will be 35 participants. With 10% increase to anticipate dropout, a total of 39-40 participants in each treatment group is required.

$$N1 = N2 = \left( \frac{Z\alpha\sqrt{2PQ} + Z\beta\sqrt{P1Q1 + P2Q2}}{P1 - P2} \right)^2$$

$Z\alpha$  (1.96), power (80%,  $Z\beta = 0.84$ ),  $P1$  based on MUST trial 44% ( $Q2 = 56\%$ ). Estimated  $P1 - P2 = 30\%$ . Thus,  $P2 = 14\%$  ( $Q2 = 86\%$ ). As 10% drop out rate is being anticipated,  $N1 = N2 = 39 \sim 40$  (total 78-80 participants)

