## 8. Randomization

After eligibility assessment, participants will be randomly assigned in a 1:1 ratio to one of the two treatment groups without stratification factors. Randomization will be performed by a dedicated research manager/assistant using block randomization (block size of 4) to ensure equal distribution between the groups.

(Note: Patients presenting with choroidal granuloma or serpiginous-like choroiditis will be directly assigned to the ATT group, in accordance with recently published guidelines coinciding with the start of this trial. Adjustments to the randomization will be made afterwards to maintain the block size)

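### The primary relative risk is unadjusted although laterality and chronicity are collected and randomisation is unstratified; prespecified adjustment for these two would be a cheap, modest gain in precision and robustness

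*Supplement*

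**What the plan says.** SAP version 2.0, section 14, items c and d, bases the primary analysis on the proportion with complete resolution at six months. The test is chi-square or Fisher's exact, and "Relative risk will be calculated and presented with 95% confidence interval in the ITT and per-protocol analysis approaches". Neither item names a covariate, and none is named for the Cox models in items c, e and f.

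Section 8 states that "participants will be randomly assigned in a 1:1 ratio to one of the two treatment groups without stratification factors", in blocks of four.

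Section 6 lists 25 baseline variables, among them "Laterality of ocular inflammation (categorical data): unilateral or bilateral" and chronicity (acute or chronic). Item 14b summarises baseline characteristics by trial group. No other use of them is stated.

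Item 14c makes the endpoint a patient-level one: a bilateral case with one unresolved eye is a non-resolution.

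Section 7 sizes the trial for the unadjusted comparison and arrives at 78 to 80 patients.

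**The concern.** With about 40 patients per arm and no stratification, the arms may differ by chance on a variable that predicts resolution. A crude relative risk carries that difference into the estimate and leaves explainable variation in its standard error.

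Laterality is a natural candidate because of the both-eyes rule: a bilateral patient has two eyes to clear and a unilateral patient one.

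The cost is some lost precision, and also some loss of credibility. If the baseline table shows a visible imbalance and no adjusted analysis was prespecified, any later adjustment can be criticised as chosen after seeing the data.

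**Working it through.** **1. The plan's own figure.** The inputs are all from SAP section 7: "for a two-sided significance level of 5% and 80% power"; "the proportion of uveitis patients with active disease at six months following treatment was found to be 44" per cent; "A 30% difference in uveitis resolution between the two groups is predetermined". So P1 = 0.44, P2 = 0.14 and mean P = 0.29.

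n = [(1.96 × √(2 × 0.29 × 0.71) + 0.84 × √(0.44 × 0.56 + 0.14 × 0.86)) / 0.30]² = 34.67, which rounds up to 35.

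This agrees with the SAP: "the estimated sample size required for each treatment group will be 35 participants". The SAP then adds "As 10% drop out rate is being anticipated", and 35 / 0.9 = 38.9, or 39 per arm. Power of the crude test is 80.3% at 35 per arm and 85.4% at 40. The planned analysis meets its target on its own assumptions.

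**2. How large chance imbalance can be.** For a factor present in half the patients, at 40 per arm:
- The SD of the between-arm difference is √(2 × 0.5 × 0.5 / 40) = 0.112.
- By the hypergeometric distribution, the arms differ by at least 10 points in 50% of randomisations and by at least 20 points in 12%.
- At 30% prevalence these become 47% and 9%.

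**3. What the both-eyes rule could imply for laterality.** Assume half the patients are bilateral and the two eyes of a patient are independent. If a single eye resolves with probability p, a bilateral patient resolves with probability p².
- Control arm: (p + p²) / 2 = 0.56 gives p = 0.67 and p² = 0.45. The gap is 22 points and the odds ratio about 2.5.
- ATT arm: (p + p²) / 2 = 0.86 gives p = 0.90 and p² = 0.82. The gap is about 9 points.

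The gap shrinks towards zero as fellow eyes become more alike. The documents give neither the share of bilateral cases nor the correlation between eyes.

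**4. Effect on the estimate.** One SD of imbalance times the 22-point gap is 0.112 × 0.22 = 0.025, or about 2.5 points. The crude standard error of the risk difference at 40 per arm is √(0.44 × 0.56 / 40 + 0.14 × 0.86 / 40) = 0.096, or 9.6 points. A typical shift is about a quarter of a standard error, and the crude interval already allows for it.

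**5. Gain from adjustment.** No prognostic strength is given, so a range is shown. If baseline covariates explain a share R² of the outcome variance, the standard error is multiplied by √(1 − R²). At 35 per arm:

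| R² (assumed) | Reduction in SE | Power |
|---|---|---|
| 0 | none | 80.3% |
| 0.05 | 2.5% | 82.4% |
| 0.10 | 5% | 84.4% |
| 0.20 | 11% | 88.5% |

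Simulation of logistic regression with marginal standardisation, with one binary covariate at 50% prevalence, 35 per arm, 56% against 86% resolved and 3,000 trials per row:

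| Covariate odds ratio (assumed) | Power, crude | Power, adjusted | SD of log RR, crude | SD of log RR, adjusted |
|---|---|---|---|---|
| 1 | 81% | 82% | 0.172 | 0.174 |
| 3 | 81% | 84% | 0.170 | 0.167 |
| 5 | 82% | 86% | 0.167 | 0.161 |
| 8 | 81% | 88% | 0.170 | 0.156 |

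Under no treatment effect the adjusted Wald test was slightly liberal, at 5.7% to 6.3%, which flatters its power by about 1 point. The crude test gave 3.7% to 5.3%. At 40 per arm, standardisation gains about 0 to 1 point at an odds ratio of 2 per covariate, 2 to 3 points at 3 and 3 to 6 points at 4.5.

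**6. How many covariates the data can carry.** Expected failures at 40 per arm are 40 × 0.44 + 40 × 0.14 = 17.6 + 5.6 = 23.2. With treatment and two covariates that is 23.2 / 3 = 7.7 failures per coefficient; with three covariates, 23.2 / 4 = 5.8.

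**The case against.** The strongest reply is that nothing is broken. Under randomisation the crude test and relative risk are valid, chance imbalance is already reflected in the interval and the type I error, and the sample size was computed for exactly this comparison. All of that stands.

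A second reply is that the documents do not show any listed variable to be a strong predictor of resolution. That also stands. The case for laterality is structural and of unknown size, since fellow eyes are correlated and the oral-steroid limit in the endpoint already applies to the whole patient. Chronicity is only plausible. A reader might take the protocol's introductory remark about severity and the decision to start ATT as evidence of prognosis. It does not support that: it describes who received ATT in a retrospective analysis, a confounding that randomisation removes.

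A third reply concerns the model. With resolution expected near 86% in one arm, a log-link model fits poorly. In simulated trials of modified Poisson regression with three covariates, at least one fitted probability exceeded 1 in 54% of trials (covariate odds ratio 1) to nearly all (4.5). Few failures are expected, so the covariate list must be short. This objection determines the form of the fix.

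What remains is that the data are already collected, the expected cost is small, and a prespecified adjusted estimate is more credible than one added after the baseline table has been seen.

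**Conclusion.** The point holds as a modest improvement. The primary relative risk is unadjusted, allocation is unstratified, and two plausibly prognostic variables are collected but unused.

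The gain at 40 per arm is about 0 to 1 point of power at an odds ratio of 2 per covariate, about 3 points at 3 and up to about 6 points at 4.5, against about 1 point lost if neither covariate is prognostic. These figures rest on assumed odds ratios, on 50% prevalence for the covariates, and on the SAP's rates of 56% and 86% resolved. At the odds ratio of about 2.5 that laterality could reach under independent eyes, the gain is small.

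Two stronger readings are not supported. A reader might infer that the crude result is biased or underpowered; the SAP's own figures reproduce and show otherwise. A reader might also infer that adjusting for posterior involvement would deal with the note in SAP section 8, under which patients with choroidal granuloma or serpiginous-like choroiditis go directly to the ATT group. That imbalance is systematic. Those patients have no randomised controls, so no covariate can supply the missing comparison, and a choroiditis term could give the false impression that the matter is settled.

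**What to change.** In SAP section 14, items c and d:
- Prespecify, for the randomised ITT patients, a relative risk adjusted for laterality and chronicity, obtained by logistic regression with marginal standardisation.
- Name the variance estimator (robust or bootstrap), because the simulated Wald test was slightly liberal.
- Report the crude relative risk with the chi-square or Fisher test beside it, and state which of the two is primary.
- Use the same two covariates in the Cox models for resolution.
- State separately how patients assigned directly to ATT are handled; the adjusted model does not cover them.

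The cost is a few lines of text and some programming, with no new data collection. The SAP names a single software package, so it should also say how the standardised estimate and its variance will be produced there, or name another program. The statistical downside is about 1 point of power if neither covariate is prognostic.

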### **Main study parameters/endpoints:**

#### Primary Outcome

- Complete resolution of uveitis at the patient level at six months.

Criteria for complete uveitis resolution (applied to both eyes: patient-level outcome): (1) fewer than or equal to 0.5+ anterior chamber cells according to the Standardized Uveitis Nomenclature (SUN) grading system, fewer than or equal to 0.5+ vitreous haze based on clinical grading using the NEI (National Eye Institute) scale, and no active retinal or choroidal lesions; and (2) no more than 7.5 mg of oral prednisone daily (i.e., methylprednisolone at 6 mg or less daily) and fewer than or equal to 2 drops of prednisolone acetate 1% (or equivalent) per day. These criteria have to be maintained for at least 90 days following the visit when the first complete uveitis resolution was recorded.

If there is insufficient follow-up after resolution, maintained uveitis resolution is still considered. Participants who meet criterion 1 but not criterion 2 will be classified as having partial uveitis resolution, and for the primary endpoint classification, they will be considered to have non-complete uveitis resolution.

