## **1.3. Hypothesis**

Patients that received initial treatment incorporating a full course of ATT in QFT-positive patients with uveitis of undetermined cause is achieving complete uveitis resolution at six months and reducing uveitis relapse during follow-up after the initial six months.

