## **5. Additional study parameters (endpoints)**

- a. Time to uveitis resolution: Calculated from the time of randomization.

Type of data: time (in months)

- b. Uveitis relapse (subsequent follow-up, beyond 6 months)

Relapse: any worsening of ocular inflammation (including a two-step increase in anterior chamber or vitreous cells as per the SUN grading system) or the occurrence of clinically new inflammatory activity (such as choroidal or retinal lesions) that necessitated a modification of local or systemic uveitis treatment after a minimum of 90 days of complete uveitis resolution at the patient level.

Type of data: Categorical

- c. Time to relapse was calculated from the first visit showing inactive uveitis until the first notification of uveitis relapse.

Type of data: time (in months)

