## 10. Study follow-up

Participants will be assessed at screening, baseline (Week 0), Week 2, and then at monthly intervals until the primary endpoint at 6 months (Month 1, Month 2, Month 3, Month 4, Month 5, and Month 6). If deemed necessary by the attending uveitis specialist or pulmonologist, visits outside this schedule will be possible while preserving blinding. The research manager will continue contacting participants for subsequent monthly visits beyond the primary endpoint at 6 months, though these visits are not mandatory. If a scheduled visit does not occur or if its results are missing, the value measured on the date closest to the target scheduled visit within a

window period of  $\pm 2$  weeks will be used. If the latest visit does not fall within the 6-month period ( $\pm 2$  weeks), the closest visit to this timeframe will be used.

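### SAP 14f compares relapse only among participants who reached complete resolution, so its hazard ratio is not a randomised comparison

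*Supplement*

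**What the plan says.** Protocol v2.0, section 1.3, pairs resolution at six months with "reducing uveitis relapse during follow-up after the initial six months". Relapse after complete resolution is a listed secondary outcome in the protocol summary and in SAP v2.0, section 2.

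The analysis is set out in SAP v2.0, section 14f: "For uveitis relapse outcomes, the analysis will include participants with complete uveitis resolution, regardless of follow-up duration". It continues: "Cox proportional hazards models, along with hazard ratio and Kaplan–Meier estimates, will be used for the analysis". Section 14i sets a general 5% significance threshold, and nothing marks the relapse comparison as descriptive. Section 9 states that every analysis is done first on the intention-to-treat population, meaning all randomised participants.

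SAP section 5b counts a relapse only "after a minimum of 90 days of complete uveitis resolution at the patient level". Section 5c sets the clock: "Time to relapse was calculated from the first visit showing inactive uveitis until the first notification of uveitis relapse".

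Follow-up after Month 6 is voluntary. Section 10 describes "subsequent monthly visits beyond the primary endpoint at 6 months, though these visits are not mandatory".

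On maintenance of resolution, the primary outcome in the protocol v2.0 summary requires the criteria to hold for at least 90 days, with the allowance "If there is insufficient follow-up after resolution, maintained uveitis resolution is still considered". The endpoint definitions in SAP section 4 and protocol section 6.1 contain no 90-day requirement.

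**The concern.** Randomisation makes the arms comparable at baseline. It does not make the resolvers in one arm comparable with the resolvers in the other. If ATT brings about resolution in patients who would otherwise stay active, those patients join the ATT side of the relapse analysis, while their control counterparts are left out. If such patients are more (or less) prone to relapse, the hazard ratio moves away from 1 even when ATT has no effect on relapse. The better ATT performs on the primary endpoint, the larger the unmatched group.

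At stake is the relapse part of the hypothesis. A hazard ratio with a p-value, reported under an intention-to-treat heading, would be read as the randomised effect of ATT on relapse.

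The time origin raises a smaller question. The clock starts at the first visit with inactive uveitis. That state is not defined as complete resolution, which also requires low steroid use. No relapse can count until 90 days of complete resolution have passed, so every participant carries some time in which an event is impossible.

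**Working it through.** **1. The plan's own figure.** SAP section 7 gives active disease of 44% (control) and 14% (ATT), Zα = 1.96 and Zβ = 0.84. With P = (0.44 + 0.14)/2 = 0.29 and Q = 0.71:

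n = [(1.96 × √(2 × 0.29 × 0.71) + 0.84 × √(0.44 × 0.56 + 0.14 × 0.86)) / 0.30]² = [(1.258 + 0.509)/0.30]² = 34.67, so 35 per arm. Then 35/0.90 = 38.9, so 39. The stated 35 and 39-40 are reproduced. No event count, effect size or power is stated for relapse.

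**2. Who enters the relapse analysis.** Taking resolution as the complement of active disease at six months (56% and 86%):

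| Per arm | Control | ATT |
|---|---|---|
| 35 | 0.56 × 35 = 19.6 | 0.86 × 35 = 30.1 |
| 40 | 0.56 × 40 = 22.4 | 0.86 × 40 = 34.4 |

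The restriction removes 44% of controls and 14% of ATT participants. If everyone who would resolve without ATT also resolves with it (an assumption), 0.30/0.86 = 35% of ATT resolvers have no counterpart in the control set. Later resolvers might also be admitted, which would change these counts, but entry would still follow randomisation.

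**3. Effect on the comparison when ATT has no effect on relapse.** Assume a relapse risk of 20% in those who resolve on either treatment, and r in those who resolve only on ATT. The control risk is 0.20. The ATT risk is (0.56 × 0.20 + 0.30 × r)/0.86.

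| r (assumed) | ATT risk | Apparent risk ratio |
|---|---|---|
| 10% | 0.142/0.86 = 0.165 | 0.83 |
| 20% | 0.172/0.86 = 0.200 | 1.00 |
| 30% | 0.202/0.86 = 0.235 | 1.17 |
| 40% | 0.232/0.86 = 0.270 | 1.35 |

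A simulation gives the same picture. It used 400,000 per arm, a latent severity driving both response and relapse, and a true relapse hazard ratio of 1. The responder-only hazard ratio was 1.00 when severity did not drive response, and 1.07 to 1.54 for severity-response correlations of 0.3 to 0.9.

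**4. Time origin.** Adding the same three event-free months to both arms left the simulated hazard ratio unchanged (1.233 before and after), because no event falls in that time and nobody leaves the risk set differently by arm. An unequal gap does matter. With a true ratio of about 1, a gap one month longer on ATT gave 0.88 and one month shorter gave 1.14. Two months gave 0.77 and 1.29. The documents do not say whether the gap would differ by arm.

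**5. Information in the responder-only test.** For an assumed hazard ratio of 0.5 and control relapse of 20-40%, 40 per arm yields about 8-17 events and 16-28% power. About 69 events would be needed for 80%.

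**6. An all-randomised alternative.** Count as success complete resolution with no relapse by a fixed time. If relapse risk is the same in both arms at 20%, 30% or 40%, the success rates are:

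- 0.56 × 0.80 = 44.8% v 0.86 × 0.80 = 68.8%
- 0.56 × 0.70 = 39.2% v 0.86 × 0.70 = 60.2%
- 0.56 × 0.60 = 33.6% v 0.86 × 0.60 = 51.6%

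Power at 40 per arm is 58%, 47% and 37%. If ATT also halves relapse from 30% to 15%, the rates are 39.2% v 0.86 × 0.85 = 73.1%, and power is 88%.

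**The case against.** Relapse is a secondary outcome under an exploratory objective. Only someone who has resolved can relapse, so a responder-only description is natural. The sample size and the primary relative risk do not depend on it. All of this stands. It limits the weight of the point, but it does not turn the hazard ratio into a randomised comparison.

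The bias figures rest on assumed relapse risks. This also stands. Equal risks give no bias and lower risks in the additional resolvers reverse it, so what is shown is a possible bias of unknown size and direction.

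The all-randomised endpoint is not a test of relapse either. Step 6 shows it rejecting in 37-58% of trials when ATT changes resolution only. It must therefore not carry a relapse-specific claim.

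Three stronger readings are tempting, and the documents do not support them:

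- **The 90-day lead-in itself biases the hazard ratio.** It does not if the lead-in is common to both arms; it only puts a flat start on the Kaplan-Meier curve.
- **Faster resolvers wait longer for Month 6, so guaranteed event-free time differs by arm.** This needs Month 6 to be a hard condition for counting a relapse. In SAP section 5b the reference to time beyond six months is part of the item's label, and the definition beneath it has no such condition.
- **Flares within 90 days are counted nowhere.** Under the protocol summary's primary outcome, and protocol section 6.2 for time to resolution, such a flare breaks maintained resolution. What remains is narrower: SAP section 4 omits the 90-day rule, so someone resolved at Month 6 who flares within 90 days may count as a success there and not as a relapse.

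**Conclusion.** The point holds for the restriction to resolvers. Section 14f conditions the only relapse comparison on an outcome the trial plans to shift by 30 percentage points, and no other section restores the randomised comparison. The switching analysis in SAP section 9 regroups by treatment received, so it does not do so either. On the planning rates about 22 of 40 controls and 34 of 40 ATT participants would enter. The apparent risk ratio with no true effect is 1.17-1.35 if the additional ATT resolvers relapse at 30-40% against 20% in the others, and 1.0 if they relapse equally. Those relapse rates are assumptions, and so is the premise that anyone resolving without ATT would also resolve with it.

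The time origin is a lesser matter. It distorts the early part of the Kaplan-Meier curve, and it biases the hazard ratio only if the gap before relapse can count differs between arms.

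The restriction in 14f does not affect the primary intention-to-treat analysis of six-month resolution.

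**What to change.** 1. Add an intention-to-treat analysis, in all randomised participants, of complete resolution without relapse at a fixed, prespecified time. State a rule for missing visits after Month 6: those visits are voluntary, and the existing carry-forward rule covers only the six-month visit. Report the result as sustained resolution, not as an effect on relapse, and tabulate never resolved, resolved then relapsed, and missing by arm.
2. Label the responder-only Cox and Kaplan-Meier results in 14f descriptive and non-randomised, and draw no conclusion about an effect on relapse from their p-value alone.
3. Start the responder-only clock at 90 days after first complete resolution. Bring SAP section 4 into line with the 90-day rule in the protocol summary, so that a flare inside that period counts as loss of resolution.

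The cost is revised SAP wording, a few derived variables and the missing-data rule. The drawbacks are that the all-randomised endpoint mixes resolution with relapse, has modest power if ATT affects resolution only, and depends on attendance at visits that are not required.
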